**Methods:**

We will conduct a large pragmatic 2 × 2 factorial cluster-randomized controlled trial across 12 hospitals in the Cleveland Clinic Health System that will test these two approaches to reducing the use of ESA in adult patients (age ≥ 18 years) with CAP. We will enroll over 12,000 patients and evaluate the independent and combined effects of routine use of rapid diagnostic testing at admission and pharmacist-led de-escalation after 48 h for clinically stable patients with negative cultures vs usual care. We hypothesize that both approaches will reduce days on ESA. Our primary outcome is the duration of exposure to ESA therapy, a key driver of antimicrobial resistance. Secondary outcomes include detection of respiratory viruses, treatment with anti-viral medications, positive pneumococcal urinary antigen test, de-escalation by 72 h from admission, re-escalation to ESA after de-escalation, total duration of any antibiotic, 14-day in-hospital mortality, intensive care unit transfer after admission, healthcare-associated *C. difficile* infection, acute kidney injury, total inpatient cost, and hospital length-of-stay.

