### Sample size and power analysis

The sample size calculations were based upon the primary outcome of reduction exposure to ESA. For Aim 1, we anticipate an average reduction of 0.3 days (SD = 3.5 days) of exposure to ESAs due to rapid diagnostic testing, based on our preliminary data. To achieve 83% power to detect this effect size at a two-sided alpha of 0.05 and an intra-cluster correlation (ICC) of 0.001, we will randomize 12 hospitals (6 in the rapid diagnostic testing arm and 6 in the control arm) with an average of 1000 patients per hospital (coefficient of variation (COV) = 0.4). This will result in a total sample size of 12,000 patients (6000 patients per arm).

For Aim 2, we will compare the six hospitals implementing pharmacist-led antimicrobial de-escalation and the other six hospitals serving as the control group. De-escalation is expected to reduce exposure to ESAs by 1 day (SD = 3), based on our preliminary data. Assuming a 50% compliance rate in the de-escalation arm, we will have > 99% power to detect this effect size at a two-sided alpha of 0.05 and an ICC of 0.005. We will also have > 99% power to detect a reduction in the rates of CDI from 1 to 0.5% and AKI from 6 to 3%, under the same assumptions. Since testing the interaction is a secondary analysis, power calculation was not performed. All power calculations were conducted using PASS 14 (Kaysville, UT).

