### Interim analyses

Safety interim analysis will be conducted every 6 months. The all-cause death incidence rate within the first 30 days of admission is calculated as the number of all-cause deaths divided by the number of eligible patients (according to inclusion and exclusion criteria) and expressed per 1000 (or 10,000 patients) per 30 days of follow-up. We will use the all-cause death incidence rate within the first 30 days of admission calculated during the 1-year period before the study onset as a baseline estimation. We will calculate incidence-rate ratios and incidence-rate differences between the four treatment groups, using the usual care group as the reference. The four treatment arms are rapid testing and de-escalation, rapid testing only, de-escalation only, and usual care (neither rapid testing nor de-escalation). If the all-cause death incidence-rate ratio or incidence-rate difference between the usual care group and any of the three intervention groups is statistically significant at a *p*-value < 0.05, the study’s Steering Committee will be notified.

Futility interim analysis will be conducted after half the data have been collected (patient *n* = 6250). At that time, we will calculate conditional power: the probability of statistical significance at the study’s completion given the date obtained so far. We will calculate the futility index as 1 − conditional power. The study will be stopped if the futility index is above 0.8 (conditional power falls below 0.2). To calculate conditional power, we will calculate current (at *n* ≥ 6250) z-statistic, using the PASS Probability Calculator. PASS 2022 implemented conditional power calculation using Jennison and Turnbull (year 2000; pages 205–208), the general upper one-sided conditional power at stage k for rejecting a null hypothesis about a parameter θ at the end of the study, given the observed test statistic, *Z*_*k*_.

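### The futility look at 6250 patients is called half the data, but half of the only exact planned total (12,000) is 6000

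*Protocol article*

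**What the plan says.** The Interim analyses section of the protocol article times the look in words, "Futility interim analysis will be conducted after half the data have been collected", and adds in brackets that this is 6250 patients. It repeats the number when it describes the calculation: "we will calculate current (at *n* ≥ 6250) z-statistic". The consequence is worded as binding: "The study will be stopped if the futility index is above 0.8 (conditional power falls below 0.2".

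The Sample size and power analysis section gives the planned size. For Aim 1, "we will randomize 12 hospitals (6 in the rapid diagnostic testing arm and 6 in the control arm"; the mean cluster size is put at 1000, and the coefficient of variation of cluster size at 0.4. The section concludes: "This will result in a total sample size of 12,000 patients (6000 patients per arm".

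The Methods part of the abstract is looser: "We will enroll over 12,000 patients".

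The article nowhere states a total of 12,500 and nowhere explains how 6250 was reached.

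**The concern.** The words and the number that time the futility look do not agree with the planned size. If the look is at half the data and the total is 12,000, it falls at 6000 patients. If it falls at 6250 and that is half, the total is 12,500. Since 6250 is printed twice, a single misprint is an unlikely explanation.

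This matters because conditional power is the chance of a significant result at the end, given the data so far. It therefore depends on how much of the trial remains. Whoever computes it at the look must enter a final size, and the article supports one figure in the sample size section and implies another in the interim section. That choice should be fixed before the interim data are seen, because the result can end the trial.

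**Working it through.** **Inputs.** From Sample size and power analysis (Aim 1): 12 hospitals, 6 against 6; average m = 1000 patients per hospital; coefficient of variation of cluster size (CV) 0.4; ICC 0.001; difference 0.3 days; SD 3.5; two-sided alpha 0.05; stated power 83%; total 12,000. From Interim analyses: look at 6250; stop if conditional power is below 0.2.

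**Step 1. Reproduce the stated power at 12,000.** With λ = m·ICC/(m·ICC + 1 − ICC) = 1/1.999 = 0.500, the design effect allowing for unequal clusters is

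DE = [1 + (m − 1)·ICC] / [1 − CV²·λ(1 − λ)] = 1.999 / (1 − 0.16 × 0.25) = 2.082.

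SE = 3.5 × √(2 × 2.082/6000) = 0.0922, and 0.3/0.0922 = 3.25. A noncentral t with 10 degrees of freedom gives power 0.834, which matches the stated 83%. A cruder form, DE = 1 + [(1 + CV²)m − 1]·ICC = 2.159, gives 0.821. So the 83% is consistent with 12,000.

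**Step 2. Does power reveal which total was meant?** At 12,500 (12,500/12 = 1041.7 per hospital) the two formulas give 0.841 and 0.827 (rounded down from 0.8275).

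| Design effect | 12,000 | 12,500 |
|---|---|---|
| Unequal-cluster efficiency form | 0.834 | 0.841 |
| 1 + [(1 + CV²)m − 1]·ICC | 0.821 | 0.827 |

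The change is under 1 point either way, and which total sits nearer 83% depends on the formula. Power does not settle the question.

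**Step 3. Timing of the look.**
- 12,000/2 = 6000, not 6250.
- 6250/12,000 = 0.521.
- 2 × 6250 = 12,500, which is 500 patients (500/12,000 = 4.2%) above the stated total.

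**Step 4. Effect on the rule, with patient counts as the time scale.** The article does not say which effect is assumed for the remaining data. Assuming the current trend continues,

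CP = Φ[(z/√t − 1.96)/√(1 − t)].

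Setting CP = 0.2 gives the boundary z = √t·[1.96 − 0.842·√(1 − t)]:
- t = 0.500 (total 12,500): z = 0.965
- t = 0.521 (total 12,000): z = 0.994

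The shift is 0.029. If the design effect is assumed for the remaining data instead, the boundaries are −0.13 and −0.03, a shift of about 0.10. If the design effect is true (drift for 83% power), the chance of stopping is 13.7% against 13.4% under the trend version, and 1.4% against 1.7% under the design-effect version.

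**Step 5. Effect on the rule, with statistical information as the time scale.** In a cluster trial, information (1/SE²) does not grow in proportion to patients. Assume all 12 hospitals contribute throughout, and use the Aim 1 ICC and CV. With the first formula, information is 80.9 at 6250 patients, 117.6 at 12,000 and 120.0 at 12,500.
- Total 12,500: t = 80.9/120.0 = 0.674, current-trend boundary z = 1.21
- Total 12,000: t = 80.9/117.6 = 0.688, current-trend boundary z = 1.24

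The second formula gives t = 0.688 and 0.701, with boundaries 1.24 and 1.26. The shift between totals is again small, about 0.02.

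**The case against.** The strongest reply is that this is a slip without consequence. The abstract allows for more than 12,000 patients. The Data analysis plan takes in all eligible patients at the randomised hospitals, and Trial status gives an anticipated end in November 2025, so the final count need not be exactly 12,000. The interim section itself words the count as a minimum. A projected accrual somewhat above the number used for power is plausible.

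That makes a harmless origin likely, and the small size is conceded. It does not remove the contradiction. The abstract's wording is compatible with 12,500 but does not state it, and the sample size section gives exactly 12,000. Nor is this a detail left to a fuller document, since both numbers are printed and conflict.

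Three stronger readings are tempting, and the document supports none of them:
- *That the 83% power has no definite sample size behind it.* It has: the sample size section ties it to 12 hospitals averaging 1000 patients, and it reproduces there (Step 1).
- *That 83% fits 12,500 better, so 12,500 was the real plan.* This depends on the design-effect formula (Step 2).
- *That the same interim result would stop the trial under one total and not under the other.* At z = 0.98, the patient-count scale gives conditional power 0.208 for 12,500 and 0.192 for 12,000, which looks like opposite decisions. But patient fraction is not information fraction in this design. On the protocol's own ICC and CV both boundaries lie at about 1.21 to 1.26, so z = 0.98 means stop under either total. The article also states no information fraction, only half the data, so it cannot be said to contradict itself on one.

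**Conclusion.** The point holds as a numerical inconsistency in an operative rule: 6250 is not half of 12,000, and the total of which it would be half is not stated. The gap is 250 patients at the look, or 500 in the total (4.2%).

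Its practical effect is small. The stopping boundary moves by about 0.03 in z on the patient-count scale, assuming the current trend, and Aim 1 power changes by less than 1 point. The z figures rest on a choice of assumed effect that the article leaves open. The information-scale figures also assume that all 12 hospitals accrue throughout at the Aim 1 ICC of 0.001. The mismatch itself rests on no assumption. It deserves correction because the rule can end the trial and the final size should not be chosen at the look.

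**What to change.** State one planned total and use it in the abstract, in Sample size and power analysis, and in Interim analyses. Two versions are consistent:
- keep 12,000 and set the futility look at 6000; or
- state 12,500 (about 1042 per hospital), keep the look at 6250, and restate the power at that size.

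In either case, say that conditional power is computed with that same total. The change is wording only, with no added patients or procedures, and should be made before the look takes place.

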### Objectives and study aims

This large, multicenter 2 × 2 factorial cluster-randomized controlled trial aims to reduce ESA use in patients with CAP by optimizing rapid pathogen detection and improving de-escalation rates following negative cultures. The study has two aims:

Aim 1: To determine the impact of comprehensive pneumococcal UAT and rapid viral molecular diagnostic assays on antimicrobial prescribing for CAP.Hypothesis 1: Comprehensive diagnostic testing will allow fewer days of ESA.Aim 2: To compare pharmacist-led de-escalation of empiric antimicrobial therapy following negative cultures to usual care.Hypothesis 2a: Pharmacist-led de-escalation will reduce the number of days of ESA use.Hypothesis 2b: Pharmacist-led de-escalation will be more effective when physicians order UAT/rapid viral testing.

The study proposal was designed following the recommendations of the Standard Protocol Items: Recommendations for Interventional Trials (SPIRIT) and their checklist is included as an Additional file [15].

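### One futility rule with an unnamed z-statistic stops the whole factorial trial, and its trigger of 6250 patients is neither half of 12,000 nor half of the information

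*Protocol article*

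**What the plan says.** Interim analyses sets the timing: "Futility interim analysis will be conducted after half the data have been collected", which it puts at 6250 patients. The calculation rests on a single statistic: "To calculate conditional power, we will calculate current (at *n* ≥ 6250) z-statistic, using the PASS Probability Calculator". The consequence is mandatory: "The study will be stopped if the futility index is above 0.8 (conditional power falls below 0.2"). The section names no aim or contrast, gives no way to combine two conditional powers, and does not say what effect is assumed for the patients still to come.

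Elsewhere the article treats the two interventions as separate questions. Objectives and study aims gives each its own hypothesis of reduced ESA days. Sample size and power analysis powers each on six hospitals against six: Aim 1 for 0.3 days (SD 3.5, ICC 0.001, 83% power) and Aim 2 for 1 day (SD 3, ICC 0.005, 50% compliance, more than 99% power). On the total it says: "This will result in a total sample size of 12,000 patients (6000 patients per arm"). The Data analysis plan makes the primary comparison one across four treatment groups, fitted with a hospital random intercept, and treats the interaction as secondary.

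**The concern.** A four-group comparison does not yield one z-statistic, and two main effects yield two. The rule therefore cannot be run without a choice that the text does not make. One possible choice lets the aim with the small expected effect end the study for the aim with the large one, and the loss of that second answer could not be undone.

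There is also a question of timing. In a cluster trial where the same hospitals recruit before and after the look, later patients reduce only the within-hospital part of the variance. Half the patients then carry more than half the information. Conditional power is sensitive to that fraction, so treating half the patients as half the information could change the decision. Finally, the trigger count does not match the stated total.

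**Working it through.** **Inputs** (Sample size and power analysis): six hospitals per margin, mean size m = 1000, COV 0.4, two-sided alpha 0.05, and the effects, SDs and ICCs given above.

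**Reproducing the stated power for Aim 1.** The design effect is DE(m) = 1 + ((1 + COV²)m − 1) × ICC = 1 + (1160 − 1) × 0.001 = 2.159. The effective n per margin is 6000/2.159 = 2779. SE = 3.5 × √(2/2779) = 0.0939. The expected final z is θ = 0.3/0.0939 = 3.195. A noncentral t on 10 df gives 82.1%, and a relative-efficiency correction for unequal clusters gives 83.4%. The stated 83% reproduces, so these inputs are a fair basis for what follows.

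**Information fraction at half the patients**, with all 12 hospitals recruiting evenly: t = [DE(1000)/6000] / [DE(500)/3000].
- ICC 0.001: DE(500) = 1 + 579 × 0.001 = 1.579; t = 2.159/(2 × 1.579) = 0.68.
- ICC 0.005: DE(1000) = 6.795 and DE(500) = 3.895; t = 6.795/(2 × 3.895) = 0.87.
- Other ICCs: 0.50 at 0, 0.61 at 0.0005, 0.77 at 0.002, 0.93 at 0.01.
- If 6250 is half of 12,500, the two planned-ICC fractions become 0.69 and 0.88.

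**Conditional power under the current trend.** CP = Φ((Z/√t − 1.96)/√(1 − t)). Setting CP = 0.2 gives the stop boundary Z = √t × (1.96 − 0.842 × √(1 − t)).

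| t used | Stop if Z is below | CP at Z = 1.0 |
|---|---|---|
| 0.50 | 0.97 | 0.22 (continue) |
| 0.68 | 1.23 | 0.09 (stop) |
| 0.87 | 1.55 | 0.006 (stop) |

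At the 0.97 boundary implied by t = 0.5, the actual conditional power is about 0.08 for t = 0.68 and 0.005 for t = 0.87. Using 0.5 overstates conditional power there, so the study stops too rarely.

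**Probability that the whole study stops if Aim 1 supplies the z-statistic** (ICC 0.001, actual t = 0.684). P = Φ(boundary − true θ × √t), where the planned effect gives 3.195 × √0.684 = 2.64.

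| True Aim 1 effect | Current trend, t = 0.5 boundary | Current trend, t = 0.68 boundary | Design effect assumed, t = 0.5 / 0.68 boundary |
|---|---|---|---|
| Planned, 0.3 days | Φ(0.97 − 2.64) = 0.05 | Φ(1.23 − 2.64) = 0.08 | 0.002 / 0.02 |
| Half of planned | 0.36 | 0.46 | 0.05 / 0.23 |
| None | Φ(0.97) = 0.83 | Φ(1.23) = 0.89 | 0.37 / 0.72 |

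The last column uses CP = Φ((Z√t + θ(1 − t) − 1.96)/√(1 − t)) with θ = 3.195, which puts the boundaries at −0.33 and 0.58. None of these probabilities depends on Aim 2's data.

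**Trigger count.** 12,000/2 = 6000, and 2 × 6250 = 12,500.

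**The case against.** The strongest reply is that the text ties the rule to no aim. A reader might infer that low conditional power for one factor is written down as enough to end both, but it is not. The section is silent on that, and on whether one factor could be withdrawn alone. This stands: the defect is an undefined comparison with a mandatory stop, and the Aim 1 figures show what one admissible reading would do. It does not remove the point, because the article itself fixes the threshold, the timing, the method and the consequence. This is a rule stated badly, not a detail left for an analysis plan.

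A reader might also infer that conditional power will be miscalculated. The article calls 6250 patients half the data, but never says that an information fraction of 0.5 enters the formula. A z-statistic and information taken from the mixed model would give the right value. The criticism is therefore conditional. Its direction also matters: using 0.5 makes stopping rarer, so it does not add to the risk that Aim 1 ends Aim 2. Correcting the fraction while keeping a single Aim 1 rule would raise the no-effect stopping probability from 0.83 to 0.89.

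A third tempting reading concerns the reference to "the general upper one-sided conditional power at stage k for rejecting a null hypothesis". Since the hypotheses are reductions, one might fear that a working intervention would look futile. The phrase only describes the general formula in the cited software, and defining the parameter as control minus intervention satisfies it. Nothing in the article suggests that the sign would be taken the wrong way, so this is not raised.

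The mismatch between 6250 and 6000 is small. The Abstract's total of more than 12,000 patients does not rule out 12,500, and the information fraction hardly moves.

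**Conclusion.** The point holds in this form. A single stopping rule with an unnamed statistic is applied to a factorial trial with two separately powered aims. It either cannot be run as written or, on one reading, lets Aim 1 decide for Aim 2. On that reading and under the current trend, the whole study stops with probability about 5–8% if rapid testing works as planned and 83–89% if it has no effect. If the design effect is assumed instead, the no-effect figure is 37–72%. The width of that range shows why the assumed effect has to be stated.

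The timing issue is secondary and conditional: half the patients is about 0.68 to 0.87 of the information, and conditional power near the boundary is overstated only if 0.5 is used. The trigger count is a minor but plain inconsistency.

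These figures assume even recruitment in all 12 hospitals, the ICCs and COV of the sample-size section, known-variance normal theory with a critical value of 1.96, and no gain from covariate adjustment.

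**What to change.** Rewrite the futility paragraph in four respects.

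1. Compute conditional power separately for the rapid-testing and de-escalation main effects, and stop the whole study only if both fall below 0.2. State what happens when only one does.
2. Take the information fraction from the mixed model for each main effect, as interim 1/SE² over projected final 1/SE².
3. State the effect assumed for the remaining data (current trend, design effect or another).
4. Reconcile the counts: hold the look at 6000, or restate the planned total as 12,500.

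Items 1 and 2 belong together, because correcting the fraction under a single Aim 1 rule would make a whole-study stop more likely.

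The drafting cost is one paragraph. The study may run longer for the sake of one factor. If a futile factor is dropped alone, the planned interaction test and Hypothesis 2b lose information, so that consequence should be accepted explicitly or the factor kept running.

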### Dissemination plans

The project’s design emphasizes the intention and plan to utilize the knowledge and products gained to improve patient care. The trial was registered at ClinicalTrials.gov before enrolling the first patient. As the study progresses, we will update the trial progress and recruitment status (not yet enrolling–enrolling–enrollment completed). To encourage the translation of the study’s results into practice, we will disseminate the findings widely through conference presentations (e.g., CHEST annual conference, *IDWeek*, Society of Hospital Medicine) and peer-reviewed publications. The large scale and pragmatic design of our study make it unique. The knowledge obtained from this study will likely inform CAP guidelines on the potential of rapid molecular diagnostic assays to reduce ESA use and the safety and efficacy of antimicrobial de-escalation following negative cultures. Additionally, study team members will collaborate with their respective professional societies. [name], who has served on various pneumonia guideline panels, will help disseminate the findings at the Infectious Disease Society of America (IDSA) and Society for Healthcare Epidemiology of America (SHEA). [name], a board of trustees member for SHEA, will assist in disseminating the findings at SHEA meetings and conferences. Authorship on any future publications utilizing trial data will be evaluated individually, contingent on the contributor’s involvement following ICJME guidelines.

## Discussion

Our large, multicenter 2 × 2 factorial cluster-randomized controlled trial will be the first to assess two strategies for reducing ESA use in patients with CAP: (a) routine rapid diagnostic testing at admission and (b) pharmacist-led de-escalation after 48 h for clinically stable patients with negative cultures. The size and randomized design of our study will allow us to establish causality between the interventions and the duration of antimicrobial exposure. The resultant reduction in antibiotic exposure should allow us to test the relationship between ESA exposure and adverse outcomes such as CDI and AKI. By demonstrating the safety of de-escalation and the harms of prolonged ESA exposure, we hope to provide strong evidence supporting the ATS/IDSA recommendations on antimicrobial de-escalation and diagnostic testing, thereby promoting their adoption by clinicians.

The study has several limitations, addressed by its design. First, physicians may resist pharmacist recommendations for de-escalation. To mitigate this, we have secured support from senior leadership at the hospital and departmental levels. Educational efforts will target all participating physicians in the intervention hospitals, and those with low adherence levels will receive feedback and targeted education from the site champion. Second, capturing secondary events, particularly those occurring after discharge, may prove difficult. To address this, we will ascertain patients' vital status from the EHR, Ohio State Death Index, or other existing registries in CCHS. Lastly, uncertainties surrounding the COVID-19 pandemic’s impact on our study exist. If the pandemic intensifies again during the study, the circulation of influenza/RSV may be affected. Even if the pandemic remains under control, infection control measures may persist (e.g., masking and social distancing during respiratory virus season, and improved ventilation). To accommodate these potential changes, our trial will include at least the two most prevalent causes of CAP, and we may consider adding other rapid diagnostic tests (e.g., atypical CAP pathogens and other viruses) if economically feasible, such as when available in a single panel at no increased cost.

In conclusion, our pragmatic cluster-randomized trial offers a rigorous design to test two approaches to reducing the use of broad-spectrum antibiotics in patients with CAP. This will enable us to establish causality and determine whether ESAs can be safely de-escalated in stable patients.

